### Randomization, allocation concealment

2.7

SPSS 25.0 will be employed to generate the random number. A specially appointed researcher will be responsible for random grouping to reduce selection bias and eliminate confounding factors. Subjects will be randomly classified into the experimental group, and the control group in the proportion of 1:1, each group will cover 90 participants. The recruiters will obtain the sequence number from the researcher responsible for assigning when eligible subjects get recruited in the trial. To further reduce the bias and prevent communication, subjects from the two groups will receive treatment in separate rooms.

To prevent researchers’ prejudice from confusing the results, the sealed envelope method will be employed to blind randomization. The distribution sequence number of subjects will be placed in the sealed and opaque envelope, so the recruiters and evaluators cannot know the allocations. To ensure strict confidentiality, the envelope will be not transparent even under strong light. To avoid confusion, the subject's name and birthdates will be written on the outside of the envelope with carbon paper. The recording of the information regarding the sealed envelope and the subject's details will be made by a video, and a copy of the outer label of the sealed letter will be attached to the group distribution card in the envelope. Afterwards, the video will be checked by another researcher to ensure that the envelopes are sealed. The whole process of opening the envelopes will be also recorded by the video as well.

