### Trial design

2.1

This study refers to a randomized, evaluator blinded, controlled, multi-center clinical trial to be conducted in Mianyang Affiliated Hospital of Chengdu University of TCM, Mianyang Third Hospital, Mianyang Anzhou Hospital, China. Eligible participants will be randomly classified into the experimental group (n = 90) and the control group (n = 90) at a ratio of 1:1. The patients will receive one of the following interventions 30 min after laparoscopic cholecystectomy, which are acupuncture and intravenous injection of granisetron. The results will abide by the Consolidated Standards of Reporting Trials (CONSORT)^[28]^ guidelines as well as Standards for Reporting Interventions in Clinical Trials for Acupuncture (STRICTA)^[29]^ and Standard Protocol Items: Recommendations for Interventional Trials (SPIRIT) guidelines.^[30]^ This study (protocol version 2.0, May 25, 2018) was registered at the Chinese Clinical Trials Registry (ChiCTR-1800016991). Figure 1 illustrates the research design and Figure 2 presents the trial schedule.

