#### Baseline data

2.11.1

The following baseline data will be recorded by the established personal information questionnaire, namely, demographic characteristics (e.g., gender, age, height, and weight), general clinical conditions (e.g., operation time, bleeding volume, anesthesia time, and intraoperative infusion volume), as well as basic vital signs (e.g., heart rate, blood oxygen, blood pressure, and respiration).

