#### Sample size calculation

2.15.1

The total sample size of the study will be calculated by the formula based on a two-group, parallel, controlled design: n = (*Z*_1−*α*/2_ + *Z*_1−*β*/2_)^2^ × (*σ*2 1 + *σ2 2*)/*δ*^2^, where n denotes the sample size of each group, *σ* represents the standard deviation, and δ indicates the clinical significance between groups. At an α = 0.05, power = 80%, and given a bilateral test, *Z* scores of *Z*_1−*α*/2_ = 1.96 and *Z*_1−*β*/2_ = 0.84 will be obtained from the *Z* score table. Eighteen subjects recruited from February 2018 to March 2018 will be recruited in the pilot trial, and the primary outcome measure will be the time to first flatus: S1 = 2.21 and S2 = 3.53. Based on preliminary trial and clinical experience, the reduction of 4 h in the time to first flatus will be defined as our clinical expectation. Accordingly, the rounded sample size in each group is n ≈78. Assuming that the dropout rate is 15%, 180 subjects (90 in each group) will be needed in the two groups.

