#### Statistical analysis

2.15.2

1.Analysis procedures sample distribution: The number of dropouts and the rate will be described and analyzed for each data set, and the reasons for any dropouts are elucidated.2.Balance comparison: The subjects’ general data will be compared to assess the comparability of the two groups.3.Efficacy analysis: The subjects’ time to first flatus will be used as the primary outcome measure to assess the efficacy and safety of acupuncture in treating PGD. The means (χ) and standard (SD) deviations will be calculated to express the outcome measure, and the experimental and control groups will be statistically compared by two independent-sample *t* tests. Eight secondary outcomes will be applied to assess the efficacy of the acupuncture. Seven of these—namely, time to first defecation, abdominal pain, dosages of analgesia pump, abdominal distention, nausea, vomiting, and gastrointestinal hormones will be described usinḡχ± SD deviation and statistically compared between groups by Repeated Measures Analysis of Variance (RMANOVA). The statistical analysis of time to first defecation will be identical to that of time to first flatus. However, before performing RMANOVA, a sphericity test will be performed to determine whether the data are suitable for analysis by RMANOVA. If the data do not conform to the conditions of sphericity condition, the degree of freedom will be corrected using factor ε before the RMANOVA is performed. The categorical measure of psychological status will be analyzed using either the rank-sum test or Spearman's rank correlation.4.Safety analysis: In accordance with the definition of adverse events, specific adverse events, their severity level, causes, and explanations will be listed. The number of adverse events, and the incidence of adverse event will be statistically described. If inter group comparison is required, the χ^2^ test or Fisher's exact test will be performed.5.Methods of statistical analysis: An independent statistician analyzed the outcome data in accordance with the principle of intention-to-treat (ITT), that is, all subjects recruited in the group will be covered. The analysis of efficacy and safety indicators will be conducted following the principle of per-protocol (PP), that is, all subjects who completed the whole trial process without major protocol violations will be included. All statistical analysis complied with ITT population, and the results of ITT analysis will be compared with PP analysis to assess the sensitivity. All missing data will be analyzed using the last observation carried forward (LOCF) interpolation method. The qualitative data will be tested for normality, according to which independent *t* test or Mann–Whitney *U* test will be performed for groups comparison. Qualitative variables will be presented by the statistical description of χ ± SD of the normal distribution data, whereas qualitative variables will be recorded as the number of cases in each category. If the quantitative variables constitute repeated measures data, RMANOVA will be adopted for comparison, and the sphericity test will be performed to ascertain the applicability of, as well as to correct the data. The categorical variables will be represented by numbers (percentages) by χ^2^ test or Fisher's exact test *P* < .05 will be considered statistically significant on both sides in all the statistical tests. SPSS 25.0 software (SPSS, SPSS Inc, Chicago, IL) will be adopted for data statistical analysis.

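### The primary comparison in this three-hospital trial is fixed as an unadjusted two-sample test; adding centre to the models would be a minor, nearly free gain in precision

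*Protocol article*

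**What the plan says.** Section 2.1 (Trial design) describes a multi-centre trial and names the sites: "Mianyang Affiliated Hospital of Chengdu University of TCM, Mianyang Third Hospital, Mianyang Anzhou Hospital, China".

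Section 2.15.2 (Statistical analysis), item 3, fixes the primary analysis of time to first flatus: "the experimental and control groups will be statistically compared by two independent-sample" t tests. Time to first defecation is treated the same way. Item 5 adds that a normality check decides between the t test and the Mann–Whitney U test. The repeated secondary outcomes go to repeated-measures ANOVA, psychological status to a rank method, and categorical data to chi-square or Fisher tests. None of these has a centre term.

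The only step that touches on imbalance is item 2, where the "general data will be compared to assess the comparability of the two groups". No adjustment follows from it. The baseline examples in section 2.11.1 are "demographic characteristics (e.g., gender, age, height, and weight), general clinical conditions (e.g., operation time, bleeding volume, anesthesia time, and intraoperative infusion volume", plus vital signs; hospital is not among them.

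On allocation, section 2.7 says "SPSS 25.0 will be employed to generate the random number" and that subjects are assigned "in the proportion of 1:1, each group will cover 90 participants". It is silent on stratification and blocking.

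**The concern.** Hospital is known at entry and is part of the design. Time to first flatus runs from the return to the ward, and patients and families help to record it, so ward routine and recording habits could plausibly shift it between hospitals. If they do, an analysis without centre leaves that variation in the error term.

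The consequence depends on how the list was built:

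- **Unstratified list.** Arms can differ in their hospital mix by chance. The t test allows for this on average, through its standard error, but does not adjust the estimate for the imbalance that actually occurred.
- **List stratified by hospital.** Hospital mix is balanced by design, but the t test still charges between-hospital variation to the error. The interval is too wide and the test rejects too rarely.

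Centre adjustment is the better choice in both cases once hospitals differ by more than a trivial amount. At stake is precision, not validity.

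**Working it through.** **Inputs from the protocol article.** Three hospitals (2.1); 90 per arm, 1:1 (2.7); SDs 2.21 h and 3.53 h, planned difference 4 h, two-sided 5% test, 80% power, 78 per arm before dropout (2.15.1).

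**Assumptions.** The share of outcome variance lying between hospitals (called ρ here) is not given; 1%, 5%, 10% and 20% are shown. The simulations use three equal centres of 60.

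**The plan's own figure.** The stated formula gives (1.96 + 0.84)² × (2.21² + 3.53²)/4² = 8.5, so 9 per arm, not 78. That mismatch is a separate matter. It is noted because it bears on which SD to trust for power (last step).

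**Standard error on the pilot SDs.** The root-mean-square SD is √((2.21² + 3.53²)/2) = 2.945 h. The unadjusted SE is 2.945 × √(2/90) = 0.439 h, and the 95% half-width is 1.96 × 0.439 = 0.860 h.

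**Loss from leaving centre out.** Adjustment removes the share ρ from the error variance, so the SE ratio, unadjusted to adjusted, is 1/√(1 − ρ). If the list is stratified, the t statistic is too small by that factor, and the actual two-sided error is 2 × [1 − Φ(1.96/√(1 − ρ))].

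| ρ (assumed) | SE ratio | Adjusted 95% half-width | Actual error of t test if stratified |
|---|---|---|---|
| 1% | 1.005 | 0.856 h | 4.9% |
| 5% | 1.026 | 0.839 h | 4.4% |
| 10% | 1.054 | 0.816 h | 3.9% |
| 20% | 1.118 | 0.770 h | 2.8% |

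On the pilot SDs, each side of the interval shortens by about 1.3 minutes at 5%, 2.6 at 10% and 5.5 at 20%.

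**A small offset.** With an unstratified list, fitting centre costs a little, because arm and centre are not exactly orthogonal. The SE rises by about √(1/(1 − 2/179)) = 1.006. At ρ = 1% this cancels the gain; at 5%, 10% and 20% the net gain is about 2.0%, 4.8% and 11.2%.

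**Check by simulation (6,000 trials per setting).** With unstratified allocation the t test kept its error at 4.7% to 5.1% for ρ from 0 to 20%. At 20% its empirical SE was 0.436 h against 0.393 h adjusted, a ratio of 1.11. With stratified allocation its error was 4.7%, 3.6% and 2.9% at 5%, 10% and 20%, in line with the formula within simulation error.

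**Power.** At 4 h and the pilot SDs, 4/0.439 = 9.1 standard errors, so power exceeds 99.9% with or without centre. If the true SD were instead about 8.9 h, which is what 78 per arm at 4 h would imply, power at 78 per arm would be 79.9% unadjusted. With centre it would be 80.3%, 81.9%, 83.9% and 87.9% at the four values of ρ.

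**The case against.** The strongest reply is that the planned test is sound. With unstratified 1:1 allocation it keeps its 5% error, and variation between hospitals, including chance imbalance, is already in its standard error. The protocol also narrows differences between hospitals: standardized ERAS care for everyone (2.9), one operation type under general anaesthesia in ASA I–II patients (2.4), a fixed acupuncture prescription (2.10) and unified training (2.14). These favour the lower end of the assumed range, where the gain is small or nil. All of this stands, and it is why the point is minor.

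It could also be said that covariates are usually left to an analysis plan. That carries less weight here: the article goes beyond silence and names the primary test, and that test cannot include centre.

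A reader might infer three stronger claims, none of which the documents support:

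- **That the randomisation is deficient because it is not stratified by hospital.** Section 2.7 says neither that it is nor that it is not, and a condensed article commonly leaves this to the full protocol. The sentence on SPSS shows no error.
- **That ignoring centre biases the result or inflates false positives.** It does neither. The error is nominal if the list is unstratified and below nominal if it is stratified.
- **That the trial loses meaningful power on its primary outcome.** On its own SDs and 4 h target it does not. For the secondary outcomes the documents give no SDs or target differences, so no gain can be calculated.

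**Conclusion.** The point holds as a minor improvement to section 2.15.2. A three-hospital trial commits its primary outcome to a two-sample test without centre, and no other stated analysis includes it. The test is valid under unstratified allocation and conservative under stratified allocation, so a centre-adjusted model is preferable either way unless hospitals hardly differ.

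The size rests on an unknown. The loss in standard error runs from nothing useful at a 1% between-centre share, through roughly 3% to 5% at shares of 5% to 10%, to about 12% at 20%. On the pilot SDs this changes the width of the interval, not the chance of detecting 4 h.

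**What to change.** In section 2.15.2, replace the two-sample t test for time to first flatus with a linear model with arm and centre as fixed factors, and report the adjusted difference with its 95% confidence interval. If a rank test is used instead, use its centre-stratified form (van Elteren). Treat time to first defecation in the same way, and add centre as a between-subject factor in the repeated-measures analyses and as a stratum in the other secondary comparisons.

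Make the change before outcome data are seen by arm. It costs 2 degrees of freedom per model (residual 176 instead of 178 for 180 patients) and at worst about 0.6% in standard error if hospitals do not differ. It needs no extra patients, visits or data beyond recording the hospital. No change to the randomisation list is proposed.

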### Blinding

2.8

Due to the characteristics of acupuncture clinical trials and the high popularity of acupuncture in China, it is unlikely to thoroughly blind subjects in this trial, nor to make acupuncturists blind in treatment allocation. As a result, acupuncturists will not be involved in the assessment, and different groups will undergo treatment in different rooms to ensure that it is impossible for participants to impact the group allocation. The evaluators and statisticians will conduct their assigned work independently and be unaware of the group allocation throughout the whole study.

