**Figure 2 F2:**
[figure not shown]
SPIRIT schedule of schedule of enrollment, interventions, and assessments. t1 is the day before surgery, t0 is the day of the surgery, t1 is 0 to 2 h after surgery, t2 is 2 to 6 h after surgery, t3 is 6 to 12 h after surgery, t4 is 12 to 24 h after surgery, t5 is 24 to 48 h after surgery, t6 is the day of the discharged, t7 is 2 weeks after patients discharged from the hospital.

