### Intervention

2.10

The treatment strategy of this study will be collectively formulated by experienced acupuncturists, surgeons and anesthesiologists. After laparoscopy, all the subjects will be fasted and in supine position without pillow, the intervention is going to be conducted once 30 min after surgery. The experimental group will receive the treatment of sterile disposable stainless-steel needles (*Huatuo* medical instruments Co. Ltd., Suzhou, China; 0.3 mm × 40 mm/0.3 mm × 25 mm). Acupoints will be located abiding by the World Health Organization Standard Acupuncture Point Locations in the Western Pacific Region.^[32]^ The fixed prescription includes *Hegu* (LI4), *Neiguan* (PC6), *Zusanli* (ST36), *Gongsun* (SP4), lateral line 2 of forehead (MS3), lateral line 3 of forehead (MS4), and middle line of vertex (MS5) (Fig. 3), all acupoints will be bilaterally selected except for middle line of vertex (MS5). The acupuncture needles will be inserted into acupoints after the routine sterilization; subsequently, it will be evenly lifted, inserted and then twisted to *Deqi* after reaching the standard depth; the operation of each acupoint will take 30 s. The needles will be maintained on the trunk and limbs for 30 min and on the head for 6 h after *Deqi*. Acupuncture will be performed by two acupuncturists registered in China and with over 3 years of clinical experience. They will receive the relevant training before the experiment, the training courses covered acupoint positioning, acupuncture operation skills and communication skills. The control group will be intervened by professional surgical nurses, the treatment will be intravenous injection of granisetron with 3 mg/3 mL (drug approval No. H20030161, Sichuan Taiji Pharmaceutical Co., Ltd).

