#### Primary outcome

2.11.2

Time to first flatus: the researcher will inform the subjects and their families to help record the interval between the time of subjects returning to the ward after the operation to the time of first flatus after operation.

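### Whole-study evaluator blinding cannot be met as written: head needles stay visible through most of t1, all of t2 and the start of t3, and time to first flatus lies outside evaluator blinding

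*Protocol article*

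**What the plan says.** The trial design section states: "This study refers to a randomized, evaluator blinded, controlled, multi-center clinical trial". The abstract and the discussion carry the same label. Section 2.8 makes it absolute for assessors: "The evaluators and statisticians will conduct their assigned work independently and be unaware of the group allocation throughout the whole study". The same section concedes for the other parties that "it is unlikely to thoroughly blind subjects in this trial, nor to make acupuncturists blind in treatment allocation".

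Section 2.10 sets the timing of treatment, "the intervention is going to be conducted once 30 min after surgery", and of needle removal: "The needles will be maintained on the trunk and limbs for 30 min and on the head for 6 h after" Deqi is obtained. Controls receive an injection of granisetron, and the discussion confirms that there is no sham acupuncture.

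The Figure 2 legend defines the windows: "t1 is 0 to 2 h after surgery, t2 is 2 to 6 h after surgery". It continues with t3 at 6 to 12 h, t4 at 12 to 24 h and t5 at 24 to 48 h. Section 2.11.3 has researchers record abdominal pain, analgesia pump dosage, abdominal distention and nausea at each of t1 to t5. Section 2.13 has a dedicated evaluator enter the result data on the paper CRF.

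For time to first flatus, section 2.11.2 says that "the researcher will inform the subjects and their families to help record the interval" from return to the ward.

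**The concern.** Evaluator blinding is the main protection against detection bias that this trial claims, since patients and acupuncturists are unblinded. If the person rating symptoms can see needles in the scalp, the claim fails for those ratings. Pain, nausea and distention are subjective scales, and an assessor's expectation can influence how they are elicited and scored.

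For the primary outcome the question is different. The time of first flatus comes from the patient and family. An evaluator who merely transcribes that time adds no protection, however well blinded. A reader who meets the evaluator-blinded label in the abstract could credit the primary result with a safeguard that does not reach it.

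**Working it through.** The protocol gives no figure to reproduce here. The check is an overlap of time intervals, all in hours after surgery.

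**Inputs**
- Start of treatment: 0.5 h (section 2.10).
- Head-needle retention: 6 h (section 2.10).
- Windows: t1 = 0–2, t2 = 2–6, t3 = 6–12, t4 = 12–24, t5 = 24–48 (Figure 2 legend).
- Assumption: the time to place needles and reach Deqi is taken as about 0. Any real insertion time moves the end of the needle period later.

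**Needle period:** 0.5 to 0.5 + 6 = 6.5 h.

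**Overlap** = min(window end, 6.5) − max(window start, 0.5), or 0 if negative.

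| Window | Overlap | Share of window |
|---|---|---|
| t1 | 2 − 0.5 = 1.5 h | 1.5/2 = 75% |
| t2 | 6 − 2 = 4 h | 4/4 = 100% |
| t3 | 6.5 − 6 = 0.5 h | 0.5/6 = 8% |
| t4, t5 | 0 h | 0% |

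The trunk and limb needles, kept for 30 min, fall only within t1.

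**What can be seen.** The scalp sites are MS3 and MS4 on both sides plus MS5 in the midline: 2 + 2 + 1 = 5. With no sham, their absence identifies a control patient as surely as their presence identifies an acupuncture patient.

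**Safeguards stated.** Three are given. Opaque envelopes (section 2.7) conceal the sequence before assignment. Keeping acupuncturists out of assessment (section 2.8) does not hide needles from anyone else. Separate treatment rooms (sections 2.7 and 2.8) are meant to limit communication and participants' influence on allocation. None conceals the needles from an assessor.

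**Who rates.** Section 2.11.3 speaks of researchers and section 2.13 of a dedicated evaluator. If they are the same people, the whole-study statement in 2.8 conflicts with the schedule. If they are different people, the t1 and t2 ratings are taken by staff for whom no blinding is stated. Either way, these ratings are not shown to be blinded.

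**Primary outcome.** Sections 2.8 and 2.11.2 together place the observation with patients who cannot be thoroughly blinded and with their families. That families know the arm is an inference from this and from the visible needles.

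**The case against.** The strongest reply is that the protocol is open about most of this. Section 2.8 limits its claim to evaluators and statisticians, and the discussion lists the missing sham and the difficulty of blinding patients as limitations. Section 2.11.2 says plainly who helps record flatus, which an evaluator could hardly observe. Concealment of needles could also be a procedural detail left to the full protocol. Much of this stands for the primary outcome: that part limits the conclusion and is not a contradiction. It does not rescue the statement about evaluators, because the article itself asserts blinding for the whole study beside a schedule that defeats it.

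A reader might infer more than the documents support:

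- **That every researcher-recorded scale is unblinded.** t4 and t5 do not overlap the needle period, and t3 does so for only half an hour. Carry-over to t3–t6 requires the same assessor to return, and nothing says that one assessor follows each patient.
- **That the room reveals the arm.** Separate rooms are described for treatment. The article does not say where assessments take place.
- **That the bias can be sized against a detectable difference at 78 per group.** The pilot SDs and that sample size do not belong together. The formula in section 2.15.1 with its own inputs gives (1.96 + 0.84)² × (2.21² + 3.53²)/4² = 7.84 × 17.345/16 = 8.5, or 9 per group. Nothing in the article indicates how large a reporting shift might be.

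**Conclusion.** The point holds in a limited form and should be fixed. As written, evaluator blinding is not secured for any bedside rating in t2, in t1 after the first 30 min, or in the first half hour of t3. Later ratings are affected only on the added assumption that the same assessor returns. The outcomes concerned are secondary: pain, distention, nausea and recorded pump dosage.

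For time to first flatus, evaluator blinding gives no protection, because the report comes from patients and families. The protocol discloses the facts but does not draw this consequence.

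The size is stated as exposure time (1.5, 4 and 0.5 h of the three windows). The documents give no basis for estimating the bias itself. The comparator, sample size and planned analysis are unaffected by this point.

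**What to change.** Reconcile section 2.8 and the evaluator-blinded label with the schedule.

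1. Have the t1 and t2 ratings taken by existing staff who are not the blinded evaluator. Alternatively, state how the needles are concealed from the assessor.
2. Place the blinded evaluator's first visit in t3 after the head needles are out. With removal at about 6.5 h, 12 − 6.5 = 5.5 h of that window remains.
3. Restate section 2.8, the abstract and the discussion so that evaluator blinding is claimed only for assessments after needle removal. Describe the t1 and t2 scales and time to first flatus as open-label reports; if the concealment option in step 1 is chosen, the claim for t1 and t2 depends on that description.
4. Optionally, have the evaluator record a guess of the allocation at t6. This would also show whether patients have disclosed their arm.

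No change to needle retention is proposed.

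The cost is mainly in wording and in who visits when. The early secondary outcomes would be openly labelled unblinded, and the headline blinding claim would be less favourable. The rater would also change between t2 and t3 within the repeated-measures comparison, in both arms alike. Patient self-completion at t1 and t2 is a less suitable route: these are the first hours after general anaesthesia, and section 2.3 allows participants who cannot read.
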